### Ethical considerations

The present study was analyzed and approved by the Research Ethics Committee of the Federal University of Rio Grande do Norte – UFRN – CAAE – 75851023.0.0000.5537 (22/12//2023). This study was also registered in the Brazilian Clinical Trials Registry – REBEC – RBR-2dfqmr2 as a clinical trial (02/26/2024).

Students will participate on a voluntary and non-profit basis, and all stages, objectives, risks and benefits of the study will be explained. Participants may withdraw from the study at any stage without prejudice, without suffering penalties or judgments of any kind.

**Evaluation registration** Registry: RBR-2dfqmr2 - *Registro Brasileiro de Ensaios Clínicos* – *REBEC* (26/02/2024). This study was approved by the Research Ethics Committee of the Universidade Federal do Rio Grande do Norte - UFRN, under CAAE No. 75851023.0.0000.5537.

## Results

The research is in its design phase, and therefore the final results, conclusions and analysis will only be determined after implementation and data collection. The expected results reflect the initial hypotheses and objectives of the study, but may be adjusted depending on the development of the research and the analysis of the data obtained throughout the process.

### Primary outcome

It is hoped that by applying the problem situation instrument, the primary result of this study will be to demonstrate that the online educational module has an equal or greater effect on the acquisition of knowledge about leadership by nursing students, compared to the conventional classroom. This knowledge covers concepts related to team engagement, organizational culture, conflict management, feedback and the concept of leadership. To measure these variables, we used the QUAPEEL questionnaire, structured with objective and quantitative items that assess both conceptual and practical aspects.

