### Data collection instrument

To evaluate the effectiveness of the module and the acquisition of knowledge by the participants, a form developed in Google forms will be used, applied as a pre-test and post-test for both the control group and the experimental group.

The data collection forms will consist of two documents. The first is the registration form with demographic characterization, which will collect personal and academic information relevant to the study; while the second is a form that will be used as a pre- and post-test containing a problem situation made up of four objective questions focused on topics such as team motivation and engagement, organizational culture, conflict management and constructive feedback, in addition to the adaptation of the Nursing Student Self-Perception Questionnaire on Exercising Leadership (QUAPEEL), developed by Cardoso, Ramos and D’Innocenzo (2014) [11].

The problem situation is made up of six objective questions, and each question contains four alternative answers. The questions in the document are: ‘Faced with the possible dismissal of nursing professionals due to the salary floor, how would you, as a leader, address this issue to keep the team motivated and engaged?’; ‘Faced with signs of stress in the team, how would you promote an organizational culture that effectively addresses work overload and preserves the well-being of professionals? ‘; ‘In an environment where conflicts can arise due to difficult ethical decisions, as a leader, how would you mediate a conflict between team members with opposing views on the allocation of scarce resources?’; ‘As a leader, how would you provide constructive feedback to team members who have made medication errors, while promoting professional development?’; ‘How do you conceptualize leadership?’; ‘Do you consider yourself a leader?’; ‘Tick the interpersonal skills you consider necessary for a leader?’

QUAPEEL is a questionnaire that measures the skills and attitudes that nurses should exercise in their leadership practice. For use in this study, the questionnaire will be adapted in the section referring to the sociodemographic question, since the instrument will be applied to students and not to nurses.

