### Data analysis

The results analyzed will be related to the evaluation of the effectiveness of the online educational module in the acquisition of knowledge about Leadership among Nursing students, and this effectiveness will be measured by means of a pre-test and a post-test, using a problem situation instrument and the QUAPEEL questionnaire.

Therefore, in addition to the age and gender of the participants, the variables to be analyzed will include the responses of the control and experimental groups, obtained by applying the instrument containing the problem situation and the *QUAPEEL* questionnaire (S4).

The collected data will be stored and processed using Microsoft Office Excel, version 2020, and Statistical Package for the Social Sciences (SPSS), version 25.0. The analysis will include both descriptive and inferential statistics, with results presented in tables and figures.

Descriptive data treatment will involve analyzing relative and absolute frequencies, mean, standard deviation, and medians according to the normality of the variables. The normality of the data distribution will be checked using appropriate statistical tests, such as the Shapiro-Wilk test or the Kolmogorov-Smirnov test.

The answers will be analyzed using the content analysis technique and the use of a frequency scale, ranging from “Never” to “Always”, aims to measure the participants’ self-perception in relation to the frequency with which they apply leadership practices in their daily lives. This approach is essential for assessing not only the presence of such practices, but also the consistency with which they are used in different scenarios. Although the focus is on frequency, the interpretation of the data allows inferences to be made about the participants’ understanding and use of leadership practices, in line with the objectives of the study.

To analyze the pre-test and post-test conditions of the study in this protocol, the tests to be used will depend on the distribution of the data. If the data is normally distributed, the Student’s t-test for paired samples will be used to compare the means of the two moments and check for statistically significant differences.

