### Secondary outcome

The secondary outcome refers to knowledge acquisition by students on the topic of Leadership, which will be assessed through an adaptation of the Nursing Student Self-Perception Questionnaire in the Exercise of Leadership (S4).

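### The primary outcome is assigned to two instruments, and the test meant to carry it is given as four, six and seven questions, so the protocol article does not define one primary score

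*Protocol article*

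**What the plan says.** Which instrument is primary:

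- Primary outcome section, opening: "It is hoped that by applying the problem situation instrument, the primary result of this study will be to demonstrate" an equal or greater effect of the online module on knowledge. The knowledge covered includes the concept of leadership.
- Primary outcome section, closing: "To measure these variables, we used the QUAPEEL questionnaire, structured with objective and quantitative items".
- Secondary outcome section: "The secondary outcome refers to knowledge acquisition by students on the topic of Leadership, which will be assessed through an adaptation" of the same questionnaire. The abstract also names the adapted questionnaire only for the secondary outcome.
- Data analysis section: effectiveness is measured with both instruments, and neither is ranked.

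What the problem situation contains, all in the Data collection instrument section:

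- "a problem situation made up of four objective questions focused on topics such as team motivation and engagement".
- "The problem situation is made up of six objective questions, and each question contains four alternative answers".
- A list of seven questions: four scenario questions, one on how leadership is conceptualised, one asking "Do you consider yourself a leader", and one tick-list of interpersonal skills.

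What QUAPEEL measures: the Data analysis section says its frequency scale captures "self-perception in relation to the frequency with which they apply leadership practices in their daily lives". The score of 0 to 100 is described in the Data collection instrument section as perception of leadership practice. That section also says the second of QUAPEEL's three parts explores knowledge about leadership.

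**The concern.** A trial with one primary question needs one primary measure, fixed before the data are seen. Here two instruments can each claim that place on the printed text, and they do not measure the same thing. One is a knowledge test. The other yields, as its only described score, a self-rating of leadership practice.

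Two things are at stake. First, an analyst could present whichever instrument gave the better result as primary and point to a sentence in the article for support. The Results section adds to this by saying that the expected results, which reflect the hypotheses and objectives, may be adjusted in the light of the data analysis. Second, if the QUAPEEL score carried the claim, a conclusion about knowledge would rest on self-perception, reported by students who, according to the Intervention section, are told which arm they are in. (The Recruitment section says they will not know.)

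Even with the instrument settled, the item count is not. A score out of four, six or seven is a different variable, and an item on self-identification cannot contribute to a count of correct answers.

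**Working it through.** The article gives no significance level, power, effect size or margin, and its sample of about 40 is one of convenience, so it has no calculated figure to reproduce. The check is a comparison of the statements, a count, and two short calculations.

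**1. Instrument for knowledge acquisition, section by section**

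| Section | Problem situation | QUAPEEL |
|---|---|---|
| Abstract | not named | secondary |
| Data analysis | used, unranked | used, unranked |
| Primary outcome, opening | primary | – |
| Primary outcome, closing | – | measures the primary variables |
| Secondary outcome | – | secondary, same construct |

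The conflict lies within the Primary outcome section itself and again between its closing sentence and the Secondary outcome section.

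**2. Item count**

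Listed questions: 4 scenario + 1 concept + 1 self-identification + 1 skills tick-list = 7. The text states four and, separately, six. The three extra questions might belong to QUAPEEL's second part. That would explain 4 + 3 = 7, but not six, and it would blur the boundary between the primary and secondary instruments.

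**3. Effect on the score**

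Assume percent correct with equal weights (the article states no rule). One item is worth 100/k points, and four correct answers give 400/k.

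| Items k | One item (100/k) | Four correct (400/k) |
|---|---|---|
| 4 | 25.0 | 100% |
| 6 | 16.7 | 66.7% |
| 7 | 14.3 | 57.1% |

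**4. Which items can be marked**

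The self-identification question clearly has no right answer: 1 of 7, about 14%. The concept and skills questions have no key in the article, but they could be given one.

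**5. False-positive risk if both instruments are read as primary**

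Assume a two-test reading at 5% each. Under independence, 1 − (1 − 0.05)² = 1 − 0.9025 = 0.0975. Whatever the dependence, the risk cannot exceed 0.05 + 0.05 = 0.10.

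**The case against.** The best defence is that most of the text does rank the instruments. The Primary outcome section opens with the problem situation, and the abstract and the Secondary outcome section both place QUAPEEL second. On that reading one closing sentence is misplaced, and a scoring key may sit in the supplement or the full protocol, which are not shown. This stands as a guide to what the authors probably intended, and it supports deleting the sentence. It does not remove the contradiction. A key held elsewhere would not say which of two printed statements governs, nor reconcile four, six and seven.

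Four stronger readings are tempting, and the article does not support them:

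- **That no primary score exists at all.** The article fails to define one. A fuller document might.
- **That three of the seven items (43%) cannot be marked.** Only the self-identification item clearly cannot. A concept question with four alternatives, or a tick-list of skills, can be keyed, and the Primary outcome section counts the concept of leadership as part of the knowledge to be measured.
- **That QUAPEEL has nothing to do with knowledge or with the trial's aims.** Its second part is said to explore knowledge, and the Discussion says the study also seeks to understand effects on leadership skills. What holds is narrower: the 0 to 100 score is described as perceived practice.
- **That the error risk reaches 18.5%.** That is 1 − 0.95⁴, counting three versions of the test plus QUAPEEL as four independent tests. The three versions would share items, so the figure is not informative.

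**Conclusion.** The article is wrong as written on its primary endpoint. It contradicts itself on the instrument and on the number of questions, and it lists at least one question that cannot enter a knowledge score. This is conflict in printed text, not detail left to an analysis plan, and it should be resolved before data are collected.

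The size is modest but real. The false-positive risk is about 9.75% instead of 5% if both instruments were treated as primary. That rests on an assumed 5% level, which the article never states, and on independence. Positively correlated scores would usually bring it lower. The percent-correct comparison rests on assumed equal weighting. The finding itself depends on neither calculation.

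**What to change.** 1. **Primary outcome section:** name the problem-situation score as the sole primary outcome and delete the closing sentence that assigns QUAPEEL to it.
2. **Data collection instrument section:** state one item count and which items are scored, with a marking key fixed before the pre-test. Exclude the self-identification item. For the concept and skills items, either supply a key or report them descriptively. If the concept item is not scored, take the concept of leadership out of the primary construct. State whether any listed question belongs to QUAPEEL's second part.
3. **Secondary outcome section:** label the QUAPEEL score of 0 to 100 as self-perceived leadership practice, not knowledge acquisition.
4. **Data analysis section:** rank the two instruments to match.

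None of this requires changing the planned pre-test and post-test measurements, which are a separate matter.

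The cost is wording, plus notice to the registry, funder and journal as the article's section on changes already promises. The Study situation section says recruitment is still being prepared, so no data need be discarded. The downside is that a score built from few items is coarse, and the plan should say so.

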### Secondary outcome

The secondary outcome refers to knowledge acquisition by students on the topic of Leadership, which will be assessed through an adaptation of the Nursing Student Self-Perception Questionnaire in the Exercise of Leadership (S4).

## Discussion

The discussion about Leadership competence has become increasingly frequent in the context of training and developing nurses [12]. With changes in educational practices involving different ways of teaching and learning, and to meet the demands of the job market, there is a need to rethink teaching and learning methods, seeking to integrate theoretical content about leadership with practical opportunities to apply these concepts.

The literature has emphasized the importance of innovative educational methods such as online modules to address gaps in conventional teaching. Recent research indicates that the use of online modules can promote significant evolution, not only in the understanding of the concept of leadership, but also in self-identification as a leader and in the development of other fundamental skills [13,14].

Online education offers a flexible and convenient environment, allowing students to engage in their training autonomously, adjusting to their individual learning needs and schedules. This approach not only favours progress at each individual’s own pace, promoting more personalized and meaningful learning, but also eliminates geographical restrictions, guaranteeing equal access to content, as long as students have an electronic device and an internet connection [7].

Studies indicate that online training modules not only enhance knowledge, but also develop essential skills for effective leadership in nursing practice. In addition, cognitive flexibility and digital literacy play a key role in enhancing the flow of learning, increasing student engagement and adaptability. These factors reinforce the potential of online modules in preparing future professionals to face the challenges of the professional context more efficiently and autonomously [15].

An online leadership course demonstrated effectiveness in developing leadership skills among nursing professionals in the Americas, with participants showing greater knowledge acquisition. These innovative educational practices allow students to develop practical and theoretical skills in a more dynamic and effective way, directly contributing to the advancement of the training of future nurses [16].

Although the online modality and conventional teaching is the central focus of this study, it is important to consider that the conditions of each approach involve differences beyond the form of content delivery. In the online module, participants will have access to video classes, e-books, podcasts, videos available on a streaming platform (Youtube), quizzes and a forum for discussion, promoting greater flexibility and autonomy in learning. The in person course, on the other hand, will offer direct interaction with the instructor through a conventional lecture with the use of a visual resource using Powerpoint.

These variables should be taken into account when analyzing future results, as they reflect specific aspects of each modality. Therefore, this study seeks not only to compare the forms of teaching, but also to understand how these approaches impact on the acquisition of knowledge and the development of leadership skills. The results could contribute to future research and educational disciplines, enabling adaptations that combine the advantages of both modalities.

Among the possible limitations of the study, it is highlighted that as it is a specific population, the sample may undergo changes due to students withdrawing from participation in the collection period, making it necessary to recalculate the sample.

### Disclosure of study results

The present study is part of an academic Master’s degree. The dissertation and its results will be presented to the scientific committee of the Universidade Federal do Rio Grande do Norte – UFRN.

### Changes in the study

Any necessary changes to the protocol will be effectively communicated and modified in the relevant parties (trial registry, funding agency and journal). Any questions about the study will be duly answered by the researchers during the initial evaluation period and during the study period.

### Study situation

This study is currently being prepared for participant recruitment.
